## Abstract

**Background:**

One anastomosis gastric bypass (OAGB) is the most common metabolic and bariatric surgery (MBS) in Israel, recognized for its effectiveness in achieving sustainable weight loss and mitigating obesity-related diseases. The metabolic outcomes of OAGB are significantly influenced by the length of the biliopancreatic limb (BPL). The objective of this study is to determine whether tailoring the BPL length to the total small bowel length (TSBL) results in more effective weight loss compared to patients undergoing OAGB with a fixed BPL of 180 cm. Efficacy and safety of this approach will also be evaluated, ensuring it does not lead to long-term morbidity or negatively impact patients’ quality of life.

**Methods:**

This multicenter, prospective, randomized trial will enroll at least 200 participants undergoing OAGB across three centers. Participants, aged 18 and older, will be randomized into two groups: one group will undergo a tailored BPL length based on TSBL (40%), while the control group will receive a standard BPL length of 180 cm. The primary endpoint is comparison of total weight loss after 1 and 3 years. Secondary endpoints include postoperative complications, quality of life, and improvements in obesity-related diseases.

**Results:**

The study will collect and analyze data as outlined in the protocol. The results will be reported upon completion of data collection and analysis.

**Conclusions:**

The TABLE-40 study will provide robust evidence on whether tailoring the BPL to 40% of TSBL offers higher weight loss outcomes compared to a fixed-length approach in OAGB. By assessing both efficacy and safety across multiple centers, the trial aims to inform best practices in limb length selection and optimize long-term outcomes for patients undergoing OAGB.

**Trial Registration:**

This study was registered at Clinicaltrials.gov (NCT06829381) on 29/1/2025.

**Graphical Abstract:**

[figure not shown]

## Introduction

One anastomosis gastric bypass (OAGB) is reported to be the 3rd most commonly performed Metabolic and Bariatric Surgery (MBS) worldwide [1]. Its rapidly growing prevalence is supported by favorable literature showing OAGB to be an effective procedure with satisfactory outcomes in terms of sustained weight loss, improvement of obesity-related diseases, and relatively low rate of weight regain [2–4].

OAGB includes the creation of a relatively long gastric pouch providing a restrictive component, and performance of a single gastro-jejunal anastomosis, providing a hypo-absorptive component. Previous studies have shown that a biliopancreatic limb (BPL) length of 150–200 cm was both effective in weight loss outcomes and minimized the risk of malnutrition [5, 6]. The length of the BPL is a significant part of defining the metabolic outcomes after OAGB. Measurement of total small bowel length (TSBL) and tailoring of the BPL according to the TSBL is a controversial topic. There are reports recommending measuring the TSBL and ensuring at least 250–300 cm common channel (CC) to reduce the risk of malnutrition [5, 7]. TSBL can vary significantly in humans and ranges from 250 to 1300 cm [8].

In recent decades, there has been a shift towards personalized medicine, tailoring medical and surgical treatment to the individual characteristics of each patient [9, 10]. It is thought that by moving away from the “one size fits all” model, personalized medicine enhances efficacy, minimizes side effects, and improves patient outcomes. It is only natural to utilize the paradigm of personalized medicine in MBS and to tailor specific procedures to the patients’ morphometrics, such as TSBL.

The effect of different BPL lengths in OAGB has been reported—Felsenreich et al. conducted a review evaluating studies reporting various limb lengths used in gastric bypass procedures [11]. Their findings indicated that alterations in BPL length have a greater influence on the risk of nutritional deficiencies than on weight loss or remission of obesity-related diseases. Based on their analysis, they recommend constructing a BPL of 150–180 cm. In cases where a BPL exceeding 200 cm is considered, they advise measuring the TSBL to ensure that the CC remains adequately long.

The outcomes of patients after OAGB with a tailored BPL length are unclear. It is possible that these patients could have higher weight loss and metabolic outcomes. The purpose of this study is to evaluate if personalized tailoring of the BPL length to TSBL is effective and safe. Our primary outcome will investigate if tailored BPL is more effective in terms of percentage of total weight loss at 3 years compared to patients undergoing OAGB with a standard BPL length. We will also record perioperative and malnutrition-related outcomes in order to investigate the safety profile of the tailored BPL arm in comparison to the standard arm. We hypothesize that tailoring the BPL length to a percentage of the TSBL in patients undergoing OAGB will result in greater total weight loss after 1 and 3 years and result in comparable safety outcomes, including perioperative and malnutrition-related complications, compared to a fixed standard BPL length. We hereby present the protocol of the *T*ailored *B*iliopancreatic *L*imb *LE*ngth to 40% of TSBL study (TABLE-40 study).

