### Secondary Outcomes

Difference in length of BPL and TSBL between the two groups.Changes in obesity-related diseases (diabetes, hypertension, dyslipidemia, sleep apnea) at 6 months and 1 year after OAGB. Remission of obesity-related diseases will be defined according to standard clinical criteria. In general, remission is considered when the patient is asymptomatic, no longer requires disease-specific medication, and relevant laboratory values are within normal limits. For example, type 2 diabetes remission will be defined as HbA1c < 6.5% without the use of antidiabetic medication, as per ADA criteria. Similar criteria will be applied for hypertension, dyslipidemia, and other obesity-related diseases, based on established clinical guidelines [16–18].Postoperative complications after OAGB—bile reflux, marginal ulcers, internal hernia, anastomotic strictures, and others—will be screened and compared.Incidence of nutritional complications (protein malnutrition, vitamin deficiencies) during the follow-up period.Changes in quality of life, as measured by the BAROS questionnaire at 6 months and 1 year post-surgery.

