### Statistical Analysis

#### Sample Size

Based on the previous literature of study cohorts which are similar to our expected study population [21–23], our hypothesis is that at 3 years the tailored group will have a 5% higher %TWL in comparison to the fixed group (40% vs. 35%). In order to detect a difference in %TWL at 3 years with a power of 0.8 and an alpha significance of < 0.05 and standard deviations of 12, 90 patients are needed in each arm for a total of 180 patients. Assuming a drop-out rate of 10%, enrollment of 198 patients is needed for sufficient power for the trial.

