### Data Analysis

Statistical analysis will be performed using IBM SPSS Statistics software version 29. Continuous variables will be presented as means ± standard deviations, and categorical variables will be presented as frequencies and percentages. Baseline characteristics of the two groups will be compared using independent *t*-tests for continuous variables and chi-square tests for categorical variables.

The primary outcome (%TWL) will be compared between the two groups using an independent *t*-test. If data are not normally distributed, a Mann–Whitney *U* test will be used. Changes in obesity-related diseases and quality of life scores will be analyzed using paired *t*-tests or Wilcoxon signed-rank tests (as appropriate) to compare pre- and post-operative values within each group. Differences between groups will be assessed using independent *t*-tests or Mann–Whitney *U* tests. The incidence of complications will be compared between the two groups using chi-square tests or Fisher’s exact tests.

Multivariable regression analysis will be used to adjust for potential confounders (e.g., baseline BMI, comorbidities) in the analysis of the primary outcome. A *p*-value of < 0.05 will be considered statistically significant.

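### Comparable safety is hypothesised, but the only stated safety analysis is a test of difference with no margin, which cannot show comparability

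*Protocol article*

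**What the plan says.** Safety is part of the trial's declared aim. The Introduction states: "The purpose of this study is to evaluate if personalized tailoring of the BPL length to TSBL is effective and safe". Its hypothesis has two halves: greater total weight loss after 1 and 3 years, and that tailoring will "result in comparable safety outcomes, including perioperative and malnutrition-related complications". The Background of the abstract goes further and speaks of "ensuring it does not lead to long-term morbidity or negatively impact patients’ quality of life".

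The Secondary Outcomes section lists postoperative complications and "Incidence of nutritional complications (protein malnutrition, vitamin deficiencies) during the follow-up period". No expected rate is given for any of them.

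For analysis, the Data Analysis section says: "The incidence of complications will be compared between the two groups using chi-square tests", with Fisher's exact test as the alternative. The decision rule for the whole section is: "A *p*-value of < 0.05 will be considered statistically significant". No margin or confidence-interval criterion for safety appears.

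The Sample Size section rests on 3-year %TWL only, "with a power of 0.8 and an alpha significance of < 0.05 and standard deviations of 12", and arrives at 90 evaluable patients per arm.

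**The concern.** The hypothesis and the analysis ask different questions. A chi-square or Fisher test takes equal risk as its null hypothesis and can only provide evidence against it. When it fails to reject, the data may be consistent with no difference, with a clinically important difference, or with both. Comparability needs a statement of how large an excess is still tolerable and an interval that excludes anything larger. The protocol provides neither, so nothing it states can support the second half of its hypothesis.

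The direction of possible nutritional harm is not symmetric. Patients with a TSBL below 450 cm are excluded, so the tailored limb is never shorter than the control limb. The Introduction also cites a review in which limb length mattered more for nutritional deficiency than for weight loss or disease remission. An excess of nutritional complications in the tailored arm is therefore the result the trial most needs to be able to describe honestly. At stake is whether a later report could call the longer limb as safe as the standard one on the strength of a non-significant p-value.

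**Working it through.** **Inputs from the protocol.** 90 evaluable patients per arm, SD 12, a 5-point difference (40% vs 35%), alpha 0.05 and power 0.8 (Sample Size); chi-square or Fisher tests at p < 0.05 (Data Analysis); exclusion of TSBL < 450 cm (Table 1); limb of 40% of TSBL against 180 cm (Intervention).

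**Assumed.** Two-sided testing, since sidedness is not stated, and the control-arm rate of nutritional complications, which is not given. A range of rates is therefore shown.

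**Step 1. The plan's own sample size.** n per arm = 2 × (1.96 + 0.842)² × 12² / 5² = 90.4, so 91 after rounding up, against the stated 90. Power at 90 is 0.798. The figure is reproduced within rounding. It concerns %TWL only, and no safety outcome enters it.

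**Step 2. Direction.** The shortest possible tailored limb is 0.40 × 450 cm = 180 cm, equal to the control length. Every other eligible tailored-arm patient has a longer one.

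**Step 3. How often a four-fold rise would be missed.** Event counts in each arm are binomial with n = 90. Power is the total probability of all pairs of counts giving p < 0.05 two-sided, and the miss rate is 1 − power.

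| Assumed control vs tailored rate | Fisher power | Fisher misses | Chi-square power (uncorrected) | Chi-square misses |
|---|---|---|---|---|
| 1% vs 4% | 0.072 | 93% | 0.225 | 78% |
| 2% vs 8% | 0.317 | 68% | 0.440 | 56% |
| 3% vs 12% | 0.555 | 45% | 0.653 | 35% |
| 5% vs 20% | 0.847 | 15% | 0.890 | 11% |

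Smaller increases are harder to detect: at 5% vs 10%, Fisher power is 0.17.

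**Step 4. Illustration without an assumed rate.** If 2 of 90 control and 8 of 90 tailored patients had the event, Fisher's p would be 0.10. With 0 and 5 events it would be 0.059. Neither is significant under the stated rule, and neither would be described as comparable by anyone looking at the counts.

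**Step 5. What 90 per arm can say by interval.** With equal true rates p, the 95% half-width for the risk difference is 1.96 × √(2p(1 − p)/90):

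- p = 2%: 1.96 × √(2 × 0.02 × 0.98/90) = 4.1 points
- p = 5%: 1.96 × √(2 × 0.05 × 0.95/90) = 6.4 points
- p = 10%: 1.96 × √(2 × 0.10 × 0.90/90) = 8.8 points

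**Step 6. What a formal claim would need.** For non-inferiority with one-sided alpha 0.025, 80% power and equal true rates, a 5-point margin needs 124, 183 or 299 per arm at 2%, 3% or 5%. A 10-point margin needs 31, 46 or 75. Both margins are illustrations only.

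**The case against.** **Nobody says p > 0.05 means comparable.** A reader might infer that the sponsor intends to accept safety by default. The document does not say so. It describes the safety outcomes as something to investigate and compare, lists them as secondary, and claims no power for them. That stands, and the misreading is a risk rather than a stated plan. The mismatch remains, because the protocol names comparability as its hypothesis and offers no other criterion for judging it.

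**The miss rate is not a fixed number.** A reader might take from the 2% vs 8% row that a four-fold rise would be missed about two times in three. That holds for Fisher's test at an assumed 2% control rate and not in general. The nutritional outcome combines protein malnutrition with vitamin deficiencies, and the Follow-Up section plans blood tests every 3–6 months, so the combined rate need not be low. At 5% vs 20% either test would usually detect the rise. Fisher is also the more conservative of the two named tests, and perioperative events could be counted in about 99 per arm as enrolled, where Fisher misses 63% at 2% vs 8%. All of this stands, and it is why the range is shown.

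**Safety reporting belongs to the SAP.** Much of the detail does. But the article itself states both the hypothesis and the test, and these two do not fit. That is not a matter of something left out.

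**A new composite endpoint and margin would be a design change.** Agreed. Neither is needed to repair the mismatch, and Step 6 shows that a tight margin could be out of reach at this size.

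**Conclusion.** The concern holds as a mismatch between a stated hypothesis and a stated analysis. The tests in Data Analysis cannot support comparable safety at any event rate, because a non-significant difference never demonstrates it. This conclusion needs no outside figure.

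The size does rest on assumptions: two-sided tests, 90 evaluable per arm and an unknown control rate. Over control rates of 1% to 5%, the chance of missing a four-fold rise runs from 93% down to 15% with Fisher and from 78% down to 11% with uncorrected chi-square. With equal true rates of 2% to 10%, the trial would estimate the risk difference to within about 4.1 to 8.8 points either way.

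The documents do not support saying that the trial will miss harm at any one rate, that nutritional events will be rare, or that the sponsor plans to read p > 0.05 as proof of safety. The change should be made because it costs little and governs what the trial may conclude about safety.

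**What to change.** In Data Analysis, report complications and nutritional outcomes as between-arm risk differences with 95% confidence intervals, and state that p > 0.05 will not be interpreted as comparable safety. The chi-square or Fisher tests can stay alongside.

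In the Introduction, do one of two things:

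- reword the safety half of the hypothesis as a descriptive comparison; or
- keep the word comparable, on the condition that it may be claimed only if the upper confidence limit for the excess risk lies below a margin that the clinical team fixes before data are seen. Otherwise the report gives the estimate and says that comparability was not shown.

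The abstract's wording about ensuring no long-term morbidity should be softened to match.

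The cost is protocol wording, with no added patients or visits. The downside is that the safety conclusion will probably have to be more modest, since 90 per arm may not exclude a tight margin.

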## Methods

### Study Design and Patient Selection

This study is designed as a prospective, multi-centered randomized controlled trial to evaluate the impact of tailored BPL length compared to a standard BPL length in patients undergoing OAGB. Participants will be recruited from three or four centers, with potential participants identified during their pre-operative screening appointments.

Eligible participants will be patients aged 18 years and older and comply with MBS indications according to local Ministry of Health guidelines (a body mass index [BMI] ≥ 40 kg/m^2^ and BMI ≥ 35 kg/m^2^ with one or more obesity related disease). Preoperative evaluation and patient education in our study are conducted in accordance with standardized guidelines issued by the local Ministry of Health. All participating centers strictly adhere to these national protocols, ensuring consistency in preoperative care.

Exclusion criteria are shown in Table 1 and include special populations such as patients under 18 years of age, pregnancy during the study period, or those lacking judgment capacity, as well as individuals with previous bariatric surgery or TSBL < 450 cm, which is measured during OAGB. Patients with severe symptomatic gastro-esophageal reflux diseases and/or Grade C, Grade D, or Barrett’s esophagus, per endoscopy, are not considered candidates for OAGB.

**Table 1 Tab1:** Exclusion criteria for patients in the TABLE-40 study

o < 18 years old
o Total small bowel length (TSBL) less than 450 cm (measured during surgery)
o Pregnancy during the study period
o History of previous bariatric surgery
o Clinically assessed cognitive impairment precluding informed consent

Informed consent will be obtained from all participants prior to enrollment, involving a detailed explanation of the study procedures, risks, and benefits, with ample time provided for consideration and questions.

Consent will be documented using a digital form via an institutional application, with a paper form available as a backup. Following consent, participants will be randomly assigned to either the tailored BPL group (40% of TSBL) or the standard BPL group (180 cm) using a computer-generated sequence to ensure balanced allocation. Block randomization will be employed to ensure balanced allocation between the study arms throughout the recruitment period. Variable block sizes will be used to minimize predictability and maintain allocation concealment. Patients are not blinded to treatment allocation as blinding was deemed impractical and potentially misleading in this context. Stratification will not be used in the randomization process, as our study population is expected to be relatively homogeneous with regard to key baseline characteristics, and randomization is anticipated to balance these across groups. While blinding of the surgical team is not feasible due to the nature of the intervention, data collection and analysis will be performed by researchers blinded to group assignment whenever possible.

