### Intervention

#### Tailored BPL Group

During surgery, the surgeon will measure the TSBL. The BPL length will be determined as 40% of the TSBL. The rationale for this approach is to ensure a common channel length of at least 250–300 cm.

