#### Surgical Technique

All surgeries will be performed laparoscopic or robotic approach by MBS surgeons at the participating centers, adhering to standardized OAGB techniques. The dissection to create the gastric pouch begins below the level of the crow’s foot, and the pouch is created using a 40 Fr bougie for calibration, with the aim of constructing a pouch of at least 15 cm in length. The ligament of Treitz is identified and the TSBL is measured by a visual estimation. The anastomosis is performed in a side-to-side manner using a linear staple (30–40 mm) and the anastomotic opening is closed using a barbed suture. A routine blue dye leak test is performed. Mesenteric defects are not closed routinely.

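### Eligibility is settled after randomisation: the small-bowel-length exclusion is judged in theatre, possibly with the arm known, and the pregnancy exclusion runs through follow-up

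*Protocol article*

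**What the plan says.** All references are to the protocol article.

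- **Order of steps.** Study Design and Patient Selection has candidates identified at pre-operative screening and consented. Then: "Following consent, participants will be randomly assigned to either the tailored BPL group (40% of TSBL) or the standard BPL group (180 cm". No other sentence fixes the moment of allocation.
- **Bowel-length exclusion.** Table 1 lists "Total small bowel length (TSBL) less than 450 cm (measured during surgery".
- **Pregnancy exclusion.** The same section and Table 1 exclude "pregnancy during the study period", not pregnancy at entry.
- **Who measures, and how.** Under the tailored arm: "During surgery, the surgeon will measure the TSBL". The same sentence appears under the standard arm. Surgical Technique adds that "the TSBL is measured by a visual estimation".
- **Blinding.** The article says that "blinding of the surgical team is not feasible due to the nature of the intervention", and also that "Patients are not blinded to treatment allocation".
- **Role of TSBL in the analysis.** Secondary Outcomes lists the between-group difference in TSBL as an outcome.
- **Allowance for losses.** Sample Size adds 10% for drop-out and nothing for participants found ineligible after randomisation.

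**The concern.** An exclusion criterion protects a randomised comparison only if it is applied before the arm is assigned, or by someone who cannot be influenced by the arm. Here the TSBL criterion appears to act after assignment. It rests on a subjective reading by the person who will carry out the assigned operation. In the tailored arm the same reading also sets the limb length. If the arm is known when the reading is taken, borderline patients could be kept or excluded at different rates in the two arms, and TSBL could no longer be trusted as a baseline variable.

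The pregnancy criterion raises the same problem of timing without the surgeon's judgement. Conception during follow-up is a post-randomisation event in unblinded patients. Applied literally, the criterion makes a participant ineligible because of something that happened after treatment.

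What is at stake is mainly the match between the groups randomised and the groups compared, and to a lesser extent the number available for analysis. A larger sample would restore the second but not the first.

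**Working it through.** **Step 1: place the passages in order.** Screening and consent come first, then random assignment, then surgery, when TSBL is measured and the 450 cm criterion applied, then follow-up to 3 years, during which pregnancy may occur. Three features of the text support this order:

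- assignment is tied to consent and not to any theatre step;
- TSBL measurement is described separately under each arm's heading, as something done to patients already allocated;
- TSBL is compared between arms as an outcome.

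No sentence holds the allocation back until TSBL is recorded.

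**Step 2: what a reading near the cut-off does in each arm.** The tailored limb is 0.40 × TSBL; the standard limb is 180 cm.

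| TSBL (cm) | Tailored limb (cm) | Standard limb (cm) |
|---|---|---|
| 440 | 176 | 180 |
| 450 | 180 | 180 |
| 460 | 184 | 180 |
| 500 | 200 | 180 |
| 600 | 240 | 180 |

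The arms coincide exactly at the cut-off. Close to it, the reading has almost the same surgical consequence in both arms. The difference grows only further away.

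**Step 3: reproduce the planned sample size.** Inputs from Sample Size: difference 5 points of %TWL (40 vs 35), SD 12, power 0.80, alpha 0.05 (two-sided assumed, since sidedness is not stated).

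n per arm = 2 × (1.960 + 0.842)² × 12² / 5² ≈ 90.4, rounded up to 91. The plan's 90 agrees within rounding; power at 90 per arm is 0.798. Enrolment: 180 × 1.10 = 198, as stated. No arithmetic error arises here.

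**Step 4: effect of exclusions on power.** Let e be the share excluded after randomisation and left out of the analysis. The article gives no value, so 5–10% is assumed for TSBL. That is 198 × 0.05 ≈ 10 to 198 × 0.10 ≈ 20 participants. With drop-out d:

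n per arm = 198 × (1 − d) × (1 − e) / 2; power = Φ(5 / (12 × √(2/n)) − 1.960).

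| Drop-out d | Excluded e | Analysable, total | Power |
|---|---|---|---|
| 10% | 0% | 178.2 | 0.794 |
| 10% | 5% | 169.3 | 0.774 |
| 10% | 10% | 160.4 | 0.751 |
| 20% | 0% | 158.4 | 0.746 |
| 20% | 5% | 150.5 | 0.724 |
| 20% | 10% | 142.6 | 0.701 |

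At the planned drop-out, the exclusions cost about 2 to 4 percentage points. The fall from 0.794 to 0.746 is due to 20% attrition alone and is a separate matter.

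Keeping 180 analysable at 10% drop-out would need 180 / (0.90 × 0.95) = 210.5, so 211 randomised, at 5% exclusion, and 180 / (0.90 × 0.90) = 222.2, so 223, at 10%.

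**Step 5: what differential exclusion could do (illustration only).** If excluded patients differ from retained ones by g points of %TWL, dropping a share e shifts that arm's mean by e × g. With 5% excluded in one arm and 15% in the other, the between-arm difference shifts by 0.10 × g: 0.5 point for g = 5 and 1.0 point for g = 10, against a target of 5. The rates and g are all assumed.

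**The case against.** The strongest reply is that the text fixes allocation only relative to consent. It does not say when the assignment reaches theatre. The statement about blinding may mean only that the surgeon must know the arm to build the limb, not that it is known before TSBL is measured. That is fair. A reader might infer that the surgeon knows the arm when estimating TSBL; the article implies this but does not state it. If practice is already to measure first, one sentence would settle the matter.

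Second, listing an exclusion criterion is not the same as saying that randomised patients who meet it leave the analysis. A reader might infer that they do, but no passage says so, and analysis sets are commonly defined in a plan not shown here. Their absence is therefore not the point. The point is the stated order of steps, and an analysis plan cannot make a reading taken with the arm known independent of the arm.

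Third, TSBL is anatomy fixed before allocation, so exclusion is balanced in expectation unless the readings themselves differ by arm. Near 450 cm the two operations are almost identical, which weakens any surgical motive to read differently. This stands, and it limits how much bias is plausible. It does not remove the route.

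Fourth, the pregnancy criterion sits beside age and capacity and may be a loosely worded screening rule. A reader might infer that pregnancy would differ by arm through weight loss; nothing in the article supports that, and it is conjecture. The wording as it stands still extends past randomisation.

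**Conclusion.** The concern holds as a risk created by the stated order of steps, not as shown bias. On the natural reading, the TSBL criterion is applied after randomisation, on a visual estimate by a surgeon who cannot be blinded and who may know the arm. The pregnancy criterion, as worded, can be met after randomisation.

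The likely cost in power is modest: from about 0.79 to 0.77–0.75 at the planned 10% drop-out, if 5–10% were excluded for TSBL and left out of the analysis. Both conditions are assumptions; the Introduction gives only a TSBL range of 250 to 1300 cm, not the share below 450 cm. A reader might put the loss at a fall to about 0.70, but that figure also needs 20% attrition, which takes power to about 0.75 with no exclusions at all. It should not be charged to this point.

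The case for change rests less on size than on the ease of closing the route: TSBL is measured in both arms already. Should-fix.

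**What to change.** 1. **Timing of allocation.** Amend Study Design and Patient Selection so that consent is taken before surgery, but the allocation is released in theatre only after TSBL has been recorded and confirmed to meet the existing criterion. Exclusion for TSBL then falls before randomisation and needs no inflation of the sample size, and TSBL becomes a true baseline variable.
2. **Pregnancy.** Reword the criterion in the text and Table 1 so that it applies at enrolment. Keep women who conceive later in their randomised arm for analysis, with a rule set in advance for weights affected by pregnancy. Some weights may still be unusable under that rule, but the participant is not removed.
3. **Participants already randomised.** Analyse them in the arm assigned. This concerns the analysis only, not which operation they receive.

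The cost is a short protocol amendment and a rewording of one criterion. No new measurement is needed and the 450 cm criterion is unchanged. The one practical burden is that the allocation must be accessed during surgery.

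### Centre is left out of the randomisation and the primary test of a three-to-four-centre trial, for a reason that does not address centre; the cost is a modest loss of precision

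*Protocol article*

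**What the plan says.** **Centres.** Under Study Design and Patient Selection: "Participants will be recruited from three or four centers". The abstract gives three centres and at least 200 participants.

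**Randomisation.** The same Methods section describes variable-size blocks: "Block randomization will be employed to ensure balanced allocation between the study arms throughout the recruitment period". Their stated purpose is balance over time, not within centre. The section then rules out stratification: "Stratification will not be used in the randomization process, as our study population is expected to be relatively homogeneous". The sentence goes on to specify what is homogeneous: "homogeneous with regard to key baseline characteristics, and randomization is anticipated to balance these across groups".

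**Analysis.** Under Data Analysis: "The primary outcome (%TWL) will be compared between the two groups using an independent *t*-test", with a Mann–Whitney test if the data are not normal. A multivariable regression is added to "adjust for potential confounders (e.g., baseline BMI, comorbidities) in the analysis of the primary outcome". Centre is named in neither the randomisation nor the analysis.

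**The concern.** The decision not to stratify is explicit and comes with a reason, so it can be judged on that reason. Similar patients do not imply similar centres. Average weight loss can also differ between centres through the surgical teams or through the laparoscopic or robotic approach, which the protocol allows. The homogeneity argument does not reach these.

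With one unstratified list, the arms are balanced overall, but a given centre may contribute noticeably more patients to one arm. If that centre's average %TWL is high or low, part of the centre difference is carried into the treatment difference. A t-test or Mann–Whitney test has no term to remove it. It also leaves the between-centre variation in the error term of a trial sized close to 80% power.

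**Working it through.** **1. The plan's sample size.** Inputs from Sample Size: difference 5 points (40% vs. 35%), SD 12, power 0.8, alpha 0.05 (two-sided assumed).

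n per arm = 2 × [12 × (1.960 + 0.842) / 5]² = 90.4.

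The stated 90 is reproduced to within rounding. It does not depend on centre. t-test power at 90 per arm is 79.4%.

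**2. How uneven can centres become?** Simulation of 20,000 sequences with 198 patients on one list. Block sizes of 4 and 6 and the centre shares are assumptions.

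| Centre shares | Gap between arms of 10 or more in some centre |
|---|---|
| Three equal | about one third of trials |
| 50/30/20% | about 29% |
| Four equal | about 33–35% |

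For scale, a gap of 10 in a centre of 66 patients is 38 against 28.

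**3. How far does this move the estimate?** Take three equal centres with mean %TWL at −m, 0 and +m around the average (assumption). The between-centre variance is 2m²/3. With 99 per arm, the chance shift in the treatment difference has SD ≈ √[(2m²/3) × (2/99)].

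| m | Between-centre variance | Share of 12² = 144 | SD of shift | 1.96 × SD |
|---|---|---|---|---|
| 2 | 2.67 | 1.9% | 0.23 | 0.45 |
| 4 | 10.67 | 7.4% | 0.46 | 0.91 |

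Simulation at m = 4 gives an SD of 0.46–0.47 and a 95th percentile of about 0.9 points, just under a fifth of the 5-point target. The full standard error of the difference at 99 per arm is 12 × √(2/99) = 1.71.

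**4. Power gained by adjusting.** If centre explains a share R² of the variance (assumption), the residual SD is 12 × √(1 − R²). Two-sided t-test power for 5 points:

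| Per arm | No adjustment | R² = 0.02 | R² = 0.05 | R² = 0.10 |
|---|---|---|---|---|
| 90 (stated) | 79.4% | 80.2% | 81.4% | 83.4% |
| 79 (20% loss) | 74.0% | 74.8% | 76.1% | 78.3% |

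The second row uses the upper end of the 10–20% loss under Follow-Up Rate: 198 × 0.80 / 2 = 79.2.

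**5. Validity.** A separate simulation (180 patients, blocks of 4, 6 or 8, between-centre SD 0 to 4 points) gave type I error near 0.05 and no average bias, with or without centre in the model. Where centre had no effect at all, including it lowered simulated power by 0.4 to 0.9 percentage points.

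**The case against.** Unstratified randomisation is valid, and the t-test's standard error already contains the between-centre variation. The confidence interval is therefore honest, only wider than it need be. This stands, and it limits the point to precision.

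The article describes common elements across centres: national preoperative protocols, a standardised operation, one recovery pathway and one follow-up schedule. These may keep centre differences small, and an 8-point spread between centres (m = 4) would exceed the treatment effect sought. This also stands, which is why the lower end of the range is shown. But the article does not offer these elements as its reason for leaving centre out.

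A reader might infer that centre imbalance will go uncorrected altogether. The text does not support that. The regression covariates are introduced as examples, so centre may yet be included, there or in an analysis plan not shown. What is fixed is that the test named for the primary outcome cannot make the correction.

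A reader might also point to bowel length ("the TSBL is measured by a visual estimation") as a reason to adjust for centre. Both arms are measured, but the estimate sets the limb length only in the tailored arm. Centre differences in estimating it would mainly make the treatment effect vary by centre. A centre main effect does not remove such an interaction, so this is no argument for the change below.

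Nor does planning to adjust for BMI and comorbidities contradict an expectation of relative homogeneity. Adjusting for prognostic variables is sensible even when the arms are expected to balance.

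**Conclusion.** The point holds as an opportunity for improvement, not as a flaw that threatens validity. The stated reason for not stratifying does not cover centre, and the named primary test cannot account for it. The likely cost is a chance shift with SD of roughly a quarter to half a %TWL point and about 1 to 4 percentage points of power. These sizes rest on assumed centre means (±2 to ±4 points) and an assumed share of variance (2–10%). The article reports no between-centre variance, and if centres do not differ there is nothing to gain.

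**What to change.** In Data Analysis, replace the unadjusted t-test as the primary %TWL comparison with a linear model containing treatment, centre as a fixed factor, and baseline BMI (already named there). Centre takes two degrees of freedom with three centres or three with four. No patients are added, the sample size stands, and the change applies however patients were randomised. The only price is the fraction of a percentage point of power lost if centre proves irrelevant.

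Optionally, for patients not yet randomised, run the planned variable-size blocks within centre and amend the sentence that rules out stratification. This needs one list per centre. It makes the next allocation slightly easier to guess in an open trial, which variable block sizes limit but do not abolish. The model change alone is enough.
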